### Interventions

#### Non-operative treatment

Treatment will consist of sling immobilization for a period of 6 weeks. Patients will remain in a shoulder immobilization sling for 6 weeks with range of motion of the elbow, hand and wrist with addition of pendulum exercises from 3 weeks. Active mobilization will occur after 6 weeks. Light activity and range of motion in physiotherapy will be permitted at this time. Restrictions will be lifted and full function permitted once range of motion and strength have recovered.

#### Operative treatment

This trial will implement a standardized operative management protocol, using the Synthes TM (Synthes Canada, Mississauga, Ont., Canada) 3.5 mm LCP proximal humerus locking plate for open reduction internal fixation. Six fellowship-trained shoulder surgeons will perform the surgical fixation. Pre-operative medical clearance will be established via anesthesia consults if required for medically complex patients. Pre-operative intravenous (IV) antibiotic prophylaxis and administration of a general anesthetic will be utilized. Beach-chair position and the standard deltopectoral approach or minimally invasive plating technique will be utilized. The reduction technique will depend on the fracture pattern but key steps include disimpaction of the humeral head with anatomic reduction of the medial calcar and tuberosities. The locking plate will be positioned posterior to the bicipital groove at a target height of 5–8 mm distal to the tip of the greater tuberosity. Additional tuberosity suture fixation to the plate will be used when warranted. Provisional fixation, plate positioning and final fixation will be assessed with intraoperative fluoroscopy to ensure adequate reduction and hardware position. The surgical incision will be examined and staples removed 10–14 days postoperatively. The postoperative rehabilitation protocol will be identical to the nonoperative protocol as per above.

### Outcome measures

Outcome measures are separated into primary and secondary as outlines below. All functional assessment scores will be completed at baseline and 3, 6, 12 and 24 months post injury. Complications and adverse events will be recorded on standardized case-report forms that will be completed immediately following the completion of the surgical procedure for patients randomized to the surgical treatment arm. At follow-up visits, clinical evaluation will be conducted to monitor for complications including infection, nerve injury, and hematoma formation or hospital re-admission.

### Primary outcome measures

#### Constant score [46]

The Constant score has been validated and normalized in comparison to disease free patients and places greater emphasis on range of motion and strength and has been adopted by the European shoulder society for functional assessment of the shoulder. The Constant Score records a variety of shoulder measurements including an objective test of strength using a spring-loaded measuring device and reflects an overall clinical functional assessment. This instrument is based on a 100-point scale.

#### The American shoulder and elbow Surgeon’s (ASES) score [47]

The ASES score is a shoulder specific assessment tool developed by the American Shoulder and Elbow Society that consists of both patient self-assessment and physician assessment. It is a patient scoring system calculated from a self-assessment portion that evaluates pain and ability to perform tasks of daily living, and a clinical assessment which tests active range of shoulder motion and strength. The patient self-evaluation is divided into pain (recorded on a visual analogue scale) and activities of daily living (ADL, recorded on a numeric scale). The overall score is an equal weight of the two self-evaluation sections and produces a score out of 100 where 100 is the better outcome. The physician assessment is divided into four segments: range of motion, physical signs, strength and instability and does not provide a score.

#### The EuroQol EQ-5D-5 L health questionnaire score as a quality of life (QoL) measure [50]

It is a generic health status questionnaire, consisting of five dimensions (mobility, self-care, usual activities, pain/discomfort, anxiety/depression) each of which can take one of five responses. It also includes a visual analogue scale for recording an individual’s rating of their current health-related quality of life (scale 0 to 100).

#### The short form PROMIS upper extremity score [48]

This score asks 16 questions related specifically to the physical function that allows for a more precise assessment of the upper limbs. The questions ask whether the participant is able to do a collection of tasks that vary in terms of difficulty of the task, such as “are you able to peel fruit?” or “are you able to use a hammer to pound a nail?” There are five possible responses per question, ranging from ‘unable to do’ to ‘without any difficulty’.

#### The IPAQ for the elderly [49]

This is a short, four question survey geared towards the elderly population that asks respondents about the kinds of physical activities they do as part of their everyday lives. The IPAQ asks how much time in the last 7 days was spent sitting, walking, doing moderate intensity physical activity, and vigorous intensity physical activity.

### Secondary outcome measures

#### Classification, displacement, angulation and quality of reduction

Pre-operative plain films will include a true AP, axillary, and Y-lateral view. Post-injury radiographs including true AP, axillary views and y-lateral views will be obtained at the first post-operative visit (or 2 weeks post immobilization in the non-operative treatment arm), 6 weeks and 3, 6, 12 and 24 months following surgery. A standard computed tomography (CT) scan of the shoulder (pre operatively in all patients and immediately post-operatively in operative treated patients) will be conducted to ensure correct determination of the true nature of the fracture (3 or 4 part fracture as per the Neer [22], the OTA/AO [54] and the Hertel [55] classifications) as well as the degree of angulation and displacement of the fracture fragments. As per the Neer [22] classification, a “part” will be defined as displacement greater than 1 cm or angulation greater than 45 degrees. The OTA/AO classification [54] will also be determined on the pre-operative CT scans and classified as type A, B or C. The Hertel classification is based on a binary descriptive system that describes five basic fracture planes and twelve fracture patterns between the head, lesser tuberosity, greater tuberosity and the shaft components [55]. Pre-operative and post-operative (in the ORIF group) CT scans will be reformatted along standardized planes to determine fracture fragment position and angulation. The neck- shaft angle will be defined as the angle between the proximal humeral metadiaphysis to a line perpendicular to a line denoting the articular margin, as described by Court-Brown et al. [56]. Adequate neck-shaft reduction will be classified as a neck-shaft angle between 120 and 140 degrees. Angles below 120 and above 140 degrees will be classified as varus and valgus malunions, respectively. The plate position will be referenced with regard to the bicipital groove and the tip of the greater tuberosity on CT scan. Proper plate position will be classified as posterior to the bicipital groove and 5–8 mm below the tip of the greater tuberosity. The proximal humerus neck-shaft angle, head alignment, fracture reduction, and the hardware position will be recorded on standardized forms. We do not expect further imaging will be required.

#### Other radiographic outcomes

Plain x-rays evaluated by an MSK radiologist will be used to determine the presence of non-union, malunion, fracture alignment, joint arthrosis and osteopenia. For the purposes of our study, nonunions will be defined as fractures that have not healed in 3 months or those with non-progressive callus formation on 3 consecutive monthly xrays [57–61]. The pre-operative films will be used to measure baseline cortical thickness of the proximal humerus on the AP shoulder view and will allow estimation of osteopenia as described by Mather et al. [62] and a baseline and final osteoarthritis grade will be determined by the method of Weinstein et al. [63].

Complications including infection, nerve injury, bleeding, intra-articular screw penetration (hardware failure), reoperation rates and hospital re-admission rates will be assessed and recorded at all follow-up visits.

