### Non-operative treatment of displaced fractures

Non-operative management of proximal humerus fractures with a period of immobilization and progressive physiotherapy is a simple, noninvasive and readily available treatment option. In a systematic review of non-operative management, Iyengar et al. [9] evaluated 12 studies (*n* = 650) [10–21], with a mean age of 65.0 years and a mean follow-up of 3.8 years (range of 1–10 years). Based on the Neer classification [22], there were 49% undisplaced or one-part (*n* = 317), 25% two-part (*n* = 165), 21% three-part (*n* = 137), and 5% four-part (*n* = 31) fractures. Although variable, all treatment protocols included a period of sling immobilization followed by progressive mobilization as tolerated. The mean rate of radiographic union was 98% (range 93–100%). Various functional outcome scores were used; with 6 studies (*n* = 272) [10, 12, 14, 19–21] showing a weighted mean Constant score of 74 (range 55–81) corresponding to a “fair” outcome. Across all studies, a 13% complication rate was reported, with varus malunion being the most common (*n* = 44 or 7%). Proximal humerus avascular necrosis was found to be uncommon (*n* = 13 or 2%) [9]. In the largest included trial, Hanson et al. reported the functional outcomes of non-operative management through a prospective evaluation of 160 patients, with 124 patients having complete 1-year follow-up. Nearly half (53.1%) were undisplaced fractures. The average Constant score was 74.3 with a mean difference between the injured and contralateral shoulder of 8.2. They found an estimated median time to definitive union of 14 weeks, and a 7% risk of delayed or nonunion. Four patients went on to require surgical fixation and 5 patients underwent arthroscopic decompression, with an eventual operation rate of 5.6% [12]. With a large focus on undisplaced fractures, these studies highlight that non-operative management of proximal humerus fractures can lead to satisfactory functional outcomes with modest complication rates. In a report of non-operative management of displaced proximal humerus fractures, Yuksel et al. reported a mean Constant score of 61.3 (*n* = 18, eight 3-part and ten 4-part; mean age of 68.2 years; mean follow-up of 3.3 years), with nonunion and osteonecrosis detected in 27.8% (*n* = 5) [23].

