### Surgical fixation of displaced fractures

Displaced proximal humerus fractures are commonly treated with open locking plate fixation [4–6, 8, 24–26]. A systematic review of 514 displaced proximal humerus fractures treated with locking plate fixation (12 included studies, average age of 62, average follow-up of 2.4 years) [27–38] showed an overall healing rate of 96.6%. The review included 34.0% two-part (*n* = 175), 44.7% three-part (*n* = 230), and 21.2% four-part (*n* = 109) fractures. Nine out of the 12 studies (*n* = 376) [27–29, 32, 33, 35–38] reported an average Constant score of 73.6 when evaluating functional outcome. When stratified for fracture classification, the Constant score was significantly less for 4-part fractures in comparison to the 2-part fractures (*p* = 0.02). The overall complication rate was 48.8% with a reoperation rate of 13.8%. With the exclusion of varus malunion, the complication rate remained high at 32.6% over the 12 studies analyzed [24]. Two other multicenter studies evaluated locking plate fixation for the treatment of displaced proximal humerus fractures reported similar Constant scores of 70.6 and 72 at a minimum of 1 year follow-up, and overall complication rates of 40 and 45% [25, 26]. The Proximal Fracture of the Humerus Evaluation by Randomisation (PROFHER) trial was another multi-centered randomized controlled trial of 250 patients > age 16 which showed no difference between operative and nonoperative management using the Oxford shoulder score and the Short Form 12 (SF-12). The complications in the surgical and nonsurgical group were reported as 24% and 18% respectively [39].

Despite the lack of superiority demonstrated, there has been a significant increase in surgical fixation of proximal humerus fractures following the introduction of locking plate technology over the last decade [40, 41]. Associated with high complication rates, open reduction and internal fixation of isolated proximal humerus fractures in the elderly has also been found to be an independent risk factor for inpatient adverse events and mortality [42].

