### Secondary objective analysis

A.ANOVAs will be used to compare the following two-year outcome measures between the two groups: ASES, EQ-5D-5 L, PROMIS and IPAQ. In addition, the incidence proportion of complications will be derived for each group, and a comparison of the two groups will be conducted for re-operation, infection, nerve injury, hematoma, hospital readmission, and intra-articular screw penetration using a chi-square analysis. Logistic regression modeling will be used to account for variables demonstrating group imbalance.B.The incidence of malunion, non-union, and osteoarthritis will be compared between groups using chi-square statistics (and odds ratios). Time to union will be determined with Kaplan-Meier curves with a log rank test for group comparisons.C.The degree of association between the degree of displacement and angulation of the fracture fragments and the Constant score will be determined. Multivariable regression analysis will be carried out to determine if an association exists between fracture angle and the degree of displacement (independent variables), and functional outcomes using the Constant score (dependent variable). If such an association is identified, area under the curve plots will be used to determine at what degree of angulation or displacement a particular treatment is indicated.D.The degree of association between the quality of surgical reduction [degree of displacement/angulation] of the fragments based on post-operative CT scan and the Constant functional outcome measure will be determined in the surgical group using a multivariable regression analysis.

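### The 3-month nonunion definition conflicts with the protocol's own 14-week median union time, and its monthly-film criterion cannot be assessed on the scheduled films

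*Protocol article*

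**What the plan says.** Four parts of the protocol article bear on this.

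- **Definition** (Other radiographic outcomes): "nonunions will be defined as fractures that have not healed in 3 months or those with non-progressive callus formation on 3 consecutive monthly xrays". The two criteria are joined by *or*, and five references are attached.
- **Expected healing** (Non-operative treatment of displaced fractures), on the largest study in the cited review: "They found an estimated median time to definitive union of 14 weeks, and a 7% risk of delayed or nonunion". On its case mix: "Nearly half (53.1%) were undisplaced fractures". The review as a whole is cited with 98% radiographic union. The locking-plate review (Surgical fixation of displaced fractures) is cited with 96.6% healing, but without a time to union.
- **Film schedule** (Classification, displacement, angulation and quality of reduction): a film at the first post-operative visit, or at 2 weeks in the non-operative arm, then at "6 weeks and 3, 6, 12 and 24 months following surgery". The paragraph ends: "We do not expect further imaging will be required".
- **Analysis** (Secondary objective analysis, item B): nonunion incidence is compared between arms by chi-square with odds ratios, and "Time to union will be determined with Kaplan-Meier curves with a log rank test for group comparisons".

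**The concern.** A nonunion outcome should separate fractures that fail to heal from those that heal. The first criterion places the cut-off about one week before the median healing time that the protocol itself cites, where many fractures would still be on their way to union. The second criterion, which might have identified stalled healing, calls for films that the plan does not schedule. In practice the first criterion would decide nearly every case.

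The reported nonunion rate would then mostly describe how fast fractures heal early on. It could not be read beside the union rates quoted in the Background, and a difference between arms could not be interpreted as a difference in failure to heal. The plan would also give one fracture two opposite labels: united in the time-to-union analysis and nonunion in the chi-square table.

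**Working it through.** **Inputs.** Cut-off of 3 months (Other radiographic outcomes). Median union time of 14 weeks and 7% delayed or nonunion (Background, non-operative section). Films at about 2 and 6 weeks, then 3, 6, 12 and 24 months (Classification, displacement, angulation and quality of reduction). The 14-week median is a literature figure without raw data, so it cannot be reproduced and is taken as given.

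**Step 1: cut-off in weeks.** 365.25 / 4 / 7 = 13.04 weeks, which is 14 − 13.04 = 0.96 weeks before the cited median.

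**Step 2: share of all fractures unhealed at the cut-off.** Let S(t) be the proportion not yet united at time t. Before the median, S(t) is at least 0.5 whatever the shape of the curve. Illustrative values with the median held at 14 weeks follow; the curve shapes are assumptions.

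| Assumed curve | S(13.04 weeks) |
|---|---|
| Exponential, 0.5^(13.04/14) | 0.524 |
| Weibull, shape 2, 0.5^((13.04/14)^2) | 0.548 |
| Weibull, shape 3 | 0.571 |
| Weibull, shape 4 | 0.593 |
| Log-normal, sigma 0.5 | 0.556 |
| Log-normal, sigma 0.3 | 0.593 |
| Log-normal, sigma 0.2 | 0.638 |

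**Step 3: share among fractures that eventually unite.** Suppose that all 7% never unite. This is conservative, because the 7% includes delayed unions. Of 100 fractures, at least 50 are unhealed at the cut-off; 50 − 7 = 43 of these will still unite, out of 93 that unite in total.

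- Distribution-free lower bound: (0.50 − 0.07) / 0.93 = 0.462.
- Exponential: (0.524 − 0.07) / 0.93 = 0.488.
- Log-normal, sigma 0.2: (0.638 − 0.07) / 0.93 = 0.611.

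So the bound is 46%, and the assumed curves give 49% to 61%.

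**Step 4: sensitivity to the film date.** If the 3-month film is taken at 12 weeks, the same curves give 55% to 78% of all fractures unhealed. If it is taken at 14 weeks, every curve gives 50%.

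**Step 5: can the monthly criterion be applied?** With films at 2, 6, 13.04, 26.1, 52.2 and 104.4 weeks, the gaps are 4, 7.0, 13.1, 26.1 and 52.2 weeks. Three consecutive monthly films need two successive gaps of about a month, and no pair qualifies. If the 2-week film in the non-operative arm is meant as 2 weeks after the 6-week sling period, films fall at 6, 8 and 13.04 weeks, with gaps of 2 and 5.0 weeks, which are not monthly either.

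**Step 6: the two analyses side by side.** Take a fracture unhealed on the 3-month film and united on the 6-month film. The definition makes it a nonunion in the chi-square table. The Kaplan-Meier analysis counts it as a union event.

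**The case against.** The best defence is that the definition is declared for this study and referenced, and that the cited sources cannot be seen here. The 14-week figure is an estimate from another study. That study was non-operative, with 53.1% undisplaced fractures, and its definition of definitive union and its film spacing are unknown; it may not match what this protocol means by healed. The margin is only about one week. All of this limits the size of the claim. It does not remove the conflict, because the protocol offers this figure as its own account of healing time and the share is still 50% with the film at 14 weeks.

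Several stronger readings are tempting and are not supported:

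- *More than half of normally healing fractures would be misclassified.* The median describes the whole cohort, including its 7% delayed or nonunions. For fractures that eventually unite, the assured figure is 46%.
- *The same share applies to both arms.* No time to union is given for plated fractures.
- *Nonunion would be overcounted by a fixed multiple of the cited 7%.* How that study defined delayed or nonunion is not shown. The Background also cites a small displaced series with nonunion and osteonecrosis in 5 of 18 (27.8%). That is closer to the trial population, though it combines two events.
- *The monthly films can never exist.* The protocol expects no further imaging but does not forbid it. They are unscheduled, not impossible. Because the criteria are joined by *or*, the second adds no false nonunions; it is simply not assessable as planned.
- *The rule would create a spurious treatment difference.* One definition applies to both arms, and the documents do not establish a direction or size for such an effect.
- *The Kaplan-Meier median would be distorted by film dates.* The article does not say how union is dated, and that detail may properly be left to the analysis plan.

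**Conclusion.** The conflict stands. The nonunion definition, the cited healing time and the film schedule cannot all be followed and still yield a rate of failure to heal. In a cohort healing like the one cited, at least half of all fractures, and at least 46% of those that eventually unite, would be labelled nonunions at 3 months. The assumed curves put these shares at 52–64% and 49–61%. The lower bounds rest only on the cited median and the 7%; the ranges rest also on the assumed curve shapes. They speak directly to non-operative care in a largely undisplaced cohort. Nothing in the documents allows a figure for the operative arm.

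Severity is moderate. Nonunion is a secondary radiographic outcome and does not enter the Constant score analysis, the sample size or the interim boundaries.

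**What to change.** Before any between-arm comparison of nonunion, amend the definition and the matching analysis text as follows.

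1. Define nonunion as absence of union at one named, already scheduled film later than 3 months. The 6-month film is one option, with the 12-month film as a sensitivity analysis. The investigators and the radiologist should settle the choice and state it.
2. Replace the monthly-film criterion with callus progression judged between consecutive scheduled films.
3. Report not united at 3 months as a separate outcome, labelled delayed union.
4. State that nonunion is a status at the named film and that a later union remains an event in the time-to-union analysis, so that the two results can be read together.

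This changes outcome wording only. It needs no extra films or visits and leaves patient management untouched. The downside is that nonunion is called later than 3 months. Making the change in advance also avoids a redefinition that would look driven by the data.

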### Compliance and loss of follow-up

Crossovers are expected in a clinical trial of this nature. If crossovers occur, patients will be analyzed in the in the group to which they were initially assigned in keeping with the intention-to-treat principle.

We will take the following measures to aid in completion of follow-up: Patients will normally reside within 90 min travelling time of their surgical center. Patients are called by the research assistant two to four days before their appointment and those who do not attend their appointment will be rescheduled. If the patient misses their re-booking then the surgeon will phone the patient to encourage their attendance. In the event that a patient chooses not to return for a follow-up, the questionnaires are mailed out with a stamped return envelope.

